### Interventions

After randomization, the participants will be prescribed 3 g of SDT or placebo drug three times a day for a total of 8 weeks, with each dose taken before or between meals with warm water.

SDT and the placebo drug are produced by Hanpoong Pharm & Foods Co., Ltd. SDT granulated extract contains 1.0 g of Poria Sclerotium, 1.0 g of Cnidii Rhizoma, 1.0 g of Cinnamomi Ramulus, 1.0 g of Rehmanniae Radix Preparata, 1.0 g of Astragali Radix, 1.0 g of Paeoniae Radix, 1.0 g of Atractylodis Rhizoma Alba, 1.0 g of Ginseng Radix Alba, 1.0 g of Angelicae Gigantis Radix, and 0.5 g of Glycyrrhizae Radix. It will be extracted from the raw materials described and concentrated to 3 g per dose. The placebo granulated extract contains 1.7 g of lactose, 1.0 g of corn starch, 0.1 g of citric acid, 0.1 g of caramel coloring, and 0.1 g of *Ssanghwa* herbal flavor per dose. It has a similar color, shape, weight, flavor, and taste to those of SDT.

### Outcome

#### Primary outcome measure

The change in the VAS score between visit 2 (baseline) and visit 4 (after treatment) will be used as the primary outcome measure. The mean difference between the change scores of the two groups will be calculated.

#### Visual Analogue Scale

The VAS score (ranging from 0 cm as no coldness to 10 cm as the maximum coldness imaginable) will be used to assess the severity of CHHF. The VAS score will be measured at every visit.

#### Secondary outcome measure

The change in the BT and WHOQOL-BREF score between visit 2 (baseline) and visit 4 (after treatment) will be used as the secondary outcome measure. The mean difference between the change scores of the two groups will be calculated.

#### BT: thermometer measurement

After 20 min of relaxation at 24 ± 2 °C, the BT will be measured by thermometer (835-T1; Testo, Lenzkirch, Germany) at acupoints PC8 and LU4 at every visit and at ST32 and LR3 at visits 2, 3, 4, and 5.

#### WHOQOL-BREF

The Korean version of the WHOQOL-BREF is comprised of a 26-item questionnaire estimating quality of life. It assesses five areas: general quality of life, psychological health, physical health, environmental health, and social relationships [16]. The WHOQOL-BREF will be conducted at visits 2, 4, and 5.

#### Safety outcome measure

The safety assessment will be performed for all subjects who have been randomized and received study medication more than once. The subjects’ vital signs and general physical status will be examined at every visit. Hematological examination (WBC, RBC, hemoglobin, platelet) and blood chemistry tests (blood urea nitrogen, creatinine, AST, ALT, gamma-glutamyl transpeptidase (γ-GTP)) will be performed at visits 1 and 4. Blood sugar test, thyroid function test (free T4, TSH), urine test, and pregnancy test (urine human chorionic gonadotropin) will be conducted at visit 1. The occurrence of adverse events (AEs) will be checked at visits 3, 4, and 5.

#### Compliance calculation

A total of 93 investigational drugs will be provided to the subjects at visit 2 and visit 3. The subjects will be asked to return the remaining investigational medications at visit 3 and visit 4 for the purpose of calculating drug compliance. The rate of compliance will be calculated as: compliance (%) = [93 – remaining products / expected intake] × 100. Clinical trials will be continued only if compliance is ≥ 70.

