### Participant withdrawal criteria

Participants who meet the criteria summarized in Table 3 will be discontinued from the trial. The subjects who are withdrawn after randomization will be followed up for outcomes. Reasons for withdrawal will be documented in case report forms (CRF) and data will be analyzed using the intention-to-treat (ITT) principle. Each site research coordinator will be responsible for making next-visit reminder phone calls to prevent a participant’s withdrawal.

**Table 3 Tab3:** Participant withdrawal criteria of the *Sipjeondaebo-tang* study

Participant withdrawal criterion	
1. Those whose medication compliance is < 70%	
2. Those who become pregnant during the study period	
3. Those who need surgery or inpatient treatment due to emergencies such as accidents or other illnesses	
4. Subject’s withdrawal of consent	
5. Subjects who have received prohibited medicines or therapies (e.g., anticoagulants, psychotropic drugs, and other drugs that may affect the symptoms of CHHF)	
6. Those who need standard treatment due to deterioration of symptoms of CHHF	
7. Occurrence of a serious adverse event	
8. Occurrence of factors making it difficult to sustain the process or investigator’s decision to terminate because of clinical trial results affected by some factors	

*CHHF* cold hypersensitivity in the hands and feet

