#### Study schedule

The items to be measured at each visit are presented in Table 4.

**Table 4 Tab4:** Study schedule for the trial

	Screening	Treatment period			Follow-up
	Visit 1 (day − 7 to − 2)	Visit 2 (day 0)	Visit 3 (day 28 ± 3)	Visit 4 (day 56 ± 3)	Visit 5 (day 84 ± 3)
Informed consent	●				
Inclusion/exclusion criteria	●				
Randomization		●			
Drug compliance			●	●	
Vital signs	●	●	●	●	●
Body measurement^a^	●	●	●	●	●
Demographic, sociological, and gynecological information^b^	●				
Medical history^c^	●	●	●	●	●
General physical examination	●	●	●	●	●
Thermometer measurement^d^	●	●	●	●	●
Visual Analogue Scale	●	●	●	●	●
Adverse event monitoring			●	●	●
Pattern Identification Questionnaire	●				
WHOQOL-BREF		●		●	●
Laboratory tests^e^	●			●	
Chest X-ray scan and ECG	●				
Medication		●	●		
Blindness test				●	

*ECG* electrocardiogram, *WHOQOL-BREF* World Health Organization Quality of Life Scale Abbreviated Version

^a^Height and weight, but only weight for visit 2 and follow-up

^b^Age, job, digestion, exercise, smoking habit, drinking habit, sleep pattern, etc.

^c^Including general medical history and history related to cold hypersensitivity in the hands and feet

^d^Temperature measurement of both PC8 and LU4 at every visit and both ST32 and LR3 at visit 2

^e^Screening: hematological examination (white blood cells, red blood cells, hemoglobin, platelet), blood chemistry test (blood urea nitrogen, creatinine, aspartate aminotransferase, alanine aminotransferase, gamma-glutamyl transpeptidase, glucose), thyroid function test (free thyroxine, thyroid-stimulating hormone), urine test, pregnancy test (urine human chorionic gonadotropin). Visit 4: hematological examination (white blood cells, red blood cells, hemoglobin, platelet), blood chemistry test (blood urea nitrogen, creatinine, aspartate aminotransferase, alanine aminotransferase, gamma-glutamyl transpeptidase)

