### Statistical analysis

#### Efficacy assessment

For the efficacy assessment of this trial, both intention-to-treat (ITT) and per-protocol (PP) analyses will be performed. Missing data will be adjusted using the last-observation-carried-forward (LOCF) imputation method on ITT analysis. For the safety assessment of this trial, PP analysis will be conducted. The continuous variables will be expressed as the mean ± SD and the nominal variables will be reported as percentages. The ITT method will include all randomly assigned subjects, regardless of any protocol violations or study dropouts. The PP method will include only the subjects who have completed the 12-week study period without any major protocol violations and who have a compliance rate of ≥ 70%. The baseline characteristics will be compared by either a chi-square test for nominal variables or analysis of variance (ANOVA) for continuous variables. For the within-group analysis, the primary and secondary outcome variables will be assessed using a paired *t* test. The between-groups analysis after 8 weeks of administration will be performed using a repeated-measure ANOVA for the primary outcome variables, and a paired *t* test for the mean difference in the VAS score between the SDT group and the placebo group. As a secondary outcome variable, the mean differences in BT and WHOQOL-BREF scores between the groups will be analyzed using a repeated-measure ANOVA for BT and an ANOVA and post-hoc analysis for the WHOQOL-BREF scores. For all non-normal distribution data, a nonparametric statistical test will be performed. SPSS for windows version 23.0 (SPSS Inc., Chicago, IL, USA) will be used for statistical analysis. The statistical significance level will be set at *P* < 0.05.

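### The per-protocol set requires completion of week 12 although the endpoints are at week 8; the compliance formula that also defines the set needs a minor correction

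*Protocol article*

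**What the plan says.** **PP set.** The Efficacy assessment section (Statistical analysis) states: "The PP method will include only the subjects who have completed the 12-week study period without any major protocol violations". It adds a compliance requirement of at least 70%. The same section plans an ITT analysis of everyone randomised, with last observation carried forward for missing values.

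**Endpoints.** The Primary outcome measure, Secondary outcome measure and Sample size calculation sections all use the change from visit 2 to visit 4. Table 4 places visit 4 at day 56 and visit 5 at day 84. Study design and setting describes visit 5 as follow-up four weeks after administration ends.

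**Compliance.** The Compliance calculation section gives "compliance (%) = [93 – remaining products / expected intake] × 100", and on supply says "A total of 93 investigational drugs will be provided to the subjects at visit 2 and visit 3". The 70% figure is used three times: for continuing ("Clinical trials will be continued only if compliance is ≥ 70"), for withdrawal in Table 3 ("Those whose medication compliance is < 70" per cent) and for entry to the PP set. The regimen in the Interventions section is "3 g of SDT or placebo drug three times a day for a total of 8 weeks".

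**The concern.** A PP analysis estimates the effect in women who were treated and measured as planned. For a week 8 endpoint, the relevant conduct is over by visit 4. Requiring completion of week 12 adds a condition on attendance after the endpoint has been recorded and after treatment has stopped.

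Two things are at stake. Valid week 8 values are discarded in a small trial. The women who remain are also selected on something that happens later, and that event could be related to response or tolerability and could differ between arms.

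The compliance percentage is the other half of the PP definition, and it also governs withdrawal. Its formula should therefore compute what it is meant to compute, over a stated period.

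**Working it through.** **1. Endpoint time against PP condition**

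| Item | Time | Where stated |
|---|---|---|
| Treatment ends | week 8 | Interventions |
| Primary and secondary endpoints | visit 2 to visit 4 (day 56) | Outcome sections; Sample size calculation |
| Between-group analysis | after 8 weeks of treatment | Efficacy assessment |
| Visit 5 | day 84, off treatment | Study design and setting; Table 4 |
| PP completion | 12 weeks | Efficacy assessment |

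Take a woman who complies fully, attends visits 2, 3 and 4, and misses visit 5. Her endpoint change is fully observed, yet the PP rule excludes her. In the ITT analysis her week 8 change is used as observed, with nothing imputed.

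**2. Scale**

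The plan gives no rate for missing visit 5 alone. As an illustration, assume the planned 13% dropout falls evenly: 30 × 0.87 = 26.1, or about 26 per arm. One, two or three such exclusions in an arm would then remove 1/26 = 3.8%, 2/26 = 7.7% or 3/26 = 11.5% of it. These counts are assumptions, not forecasts.

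**3. The compliance formula**

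The article gives no computed compliance value to reproduce. Let R be the doses returned and E the doses expected. At three doses a day, 28 days gives E = 84. The window in Table 4, "Visit 3 (day 28 ± 3" days), allows 25 to 31 days, so E runs from 75 to 93.

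As printed, (93 − R/E) × 100:
- none returned: 93 × 100 = 9,300%
- R = 9, E = 84 (every expected dose taken): (93 − 9/84) × 100 = 9,289%
- R = 93, E = 84 (no dose taken): (93 − 93/84) × 100 = 9,189%
- R = 93, E = 75: (93 − 93/75) × 100 = 9,176%

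The range at visit 3 is therefore 9,176% to 9,300%. At visit 4 it is much the same. The shortest second interval that the windows allow is day 31 to day 53, or 22 days, so E = 66 and the minimum is (93 − 93/66) × 100 = 9,159%.

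With the bracket closed before the division, (93 − R)/E × 100 and E = 84:
- R = 9: 84/84 = 100%
- R = 34: 59/84 = 70.2%
- R = 35: 58/84 = 69.0%
- R = 93: 0%

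This is a usable percentage with a working cut-off.

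**4. Supply and period**

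Eight weeks at three doses a day is 56 × 3 = 168 doses. A supply of 93 in all would cap compliance at 93/168 = 55.4%. The number 93 equals 31 × 3, which fits one 28-day interval plus the 3-day window. Two such dispensings would be 186.

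The period matters as well. With two equal intervals at 60% and 85%, the first fails a 70% criterion applied per interval, while the 8-week figure of (60 + 85)/2 = 72.5% passes.

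**The case against.** **On the PP set.** The trial is defined as lasting 12 weeks, and the VAS, temperature and quality of life are all collected at visit 5, so a set of full completers is coherent, if strict. It would also suit a repeated-measures ANOVA that includes visit 5; the article does not list the visits in that model. This stands for analyses that use visit 5 data. It does not justify applying the condition to a change that is complete at visit 4. A reader might infer that the primary result loses data. It does not: the ITT analysis retains these women, and only the PP analysis is affected.

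**On the formula.** A reader might infer that the 70% rule cannot operate, with nobody failing under the printed formula or everybody failing under a total supply of 93. The documents do not support this. The intended calculation is plain, no site would compare 9,289% with 70%, and the schedule and visit window point to 93 per dispensing. A stacked fraction flattened in text extraction could even produce the printed string. These objections stand, and they reduce this part to a clerical correction. The period to which the criterion applies remains unstated whichever way the bracket is read.

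**Conclusion.** The PP definition does not match the endpoints it serves. As written, it excludes compliant women with valid week 8 data because of an event after the endpoint, and nothing elsewhere in the article corrects this. The effect is confined to the PP analysis of a 60-subject pilot. Its size depends on how many women reach visit 4 and miss only visit 5, which is not known. Bias, as distinct from lost precision, would arise only if missing visit 5 were related to outcome; the article neither shows this nor rules it out.

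The formula is misbracketed as printed and the supply sentence is loosely worded. Both are minor, and neither means that the compliance rule fails in practice. The 70% threshold itself is not questioned here.

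**What to change.** - **PP set (main change).** For the week 8 endpoints, define the PP set by completion through visit 4, no major protocol violation, and the compliance criterion already stated. Keep the 12-week condition only for analyses that use visit 5 data.
- **Formula (minor).** Write compliance (%) = (dispensed − returned) / expected intake × 100.
- **Supply and period (minor).** Reconcile the sentence on 93 items at visits 2 and 3 with the 168 doses that the regimen implies. State whether the 70% criterion applies to each interval or to the whole 8 weeks. That choice is the sponsor's.

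The cost is a few sentences. No new data are needed, since returns and visit attendance are already recorded. The article reports 50 participants recruited and recruitment still open, so the change can be made and dated before database lock and unblinding.

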#### AE reporting

The investigators should educate the subjects to report any AEs that occur after administration. All adverse events that occur after the start of this trial should be recorded in the case report form whether or not they are related to the test agent. All AEs will be evaluated for causal relationships. When SAEs occur, the researchers are required to notify the Institutional Review Board (IRB) and regulatory authorities within 24 h.

#### Sample size calculation

The change in the VAS score between visit 2 (baseline) and visit 4 (after treatment) will be used as the primary outcome measure. The hypotheses are as follows:H0: δ = Δ1 – Δ2 = 0H1: δ = Δ1 – Δ2 ≠ 0

where Δ1 is the average change in the VAS score between visit 4 and visit 2 in the SDT group, and Δ2 is the average change in the VAS score between visit 4 and visit 2 in the placebo group

Based on a similar study [17], the expected average VAS score difference in the SDT group is 11.85 (larger than 10, because in the study used as a reference a 100-mm VAS was applied to assess severity of CHHF, and the scores ranged from 0 to 100), and the standard deviation (SD) is estimated to be 15.255 using the pooled standard deviation formula. Considering a dropout rate of 13%, which is agreed among medical experts, we need to recruit 30 subjects per arm to calculate the treatment efficacy, and to offer the power calculation for a future large-scale RCT.

### Statistical analysis

#### Efficacy assessment

For the efficacy assessment of this trial, both intention-to-treat (ITT) and per-protocol (PP) analyses will be performed. Missing data will be adjusted using the last-observation-carried-forward (LOCF) imputation method on ITT analysis. For the safety assessment of this trial, PP analysis will be conducted. The continuous variables will be expressed as the mean ± SD and the nominal variables will be reported as percentages. The ITT method will include all randomly assigned subjects, regardless of any protocol violations or study dropouts. The PP method will include only the subjects who have completed the 12-week study period without any major protocol violations and who have a compliance rate of ≥ 70%. The baseline characteristics will be compared by either a chi-square test for nominal variables or analysis of variance (ANOVA) for continuous variables. For the within-group analysis, the primary and secondary outcome variables will be assessed using a paired *t* test. The between-groups analysis after 8 weeks of administration will be performed using a repeated-measure ANOVA for the primary outcome variables, and a paired *t* test for the mean difference in the VAS score between the SDT group and the placebo group. As a secondary outcome variable, the mean differences in BT and WHOQOL-BREF scores between the groups will be analyzed using a repeated-measure ANOVA for BT and an ANOVA and post-hoc analysis for the WHOQOL-BREF scores. For all non-normal distribution data, a nonparametric statistical test will be performed. SPSS for windows version 23.0 (SPSS Inc., Chicago, IL, USA) will be used for statistical analysis. The statistical significance level will be set at *P* < 0.05.

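### The one primary VAS hypothesis gets two between-group tests in two unranked analysis sets, all at P < 0.05, and none is named as deciding

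*Protocol article*

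**What the plan says.** Under Sample size calculation, the protocol article defines one primary outcome, "The change in the VAS score between visit 2 (baseline) and visit 4 (after treatment) will be used as the primary outcome measure", and one pair of hypotheses, "H0: δ = Δ1 – Δ2 = 0H1: δ = Δ1 – Δ2 ≠ 0". Primary outcome measure names the matching contrast: "The mean difference between the change scores of the two groups will be calculated".

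Statistical analysis (Efficacy assessment) adds three things:

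- **Two analysis sets.** "For the efficacy assessment of this trial, both intention-to-treat (ITT) and per-protocol (PP) analyses will be performed". ITT uses last observation carried forward (LOCF). PP keeps women who complete 12 weeks without a major violation and with at least 70% compliance.
- **Two between-group procedures for VAS.** The comparison is made "using a repeated-measure ANOVA for the primary outcome variables, and a paired" t test on the difference between SDT and placebo. Neither the ANOVA term (group, or group by time) nor the visits entered are given. VAS is recorded at every visit.
- **One level.** "The statistical significance level will be set at *P* < 0.05".

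No section names a deciding test or set, asks for agreement, or adjusts the level. Participant withdrawal criteria applies the ITT principle to withdrawn women, but does not rank ITT above PP.

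**The concern.** A 5% level belongs to one test in one population. Here one null hypothesis receives at least four P values: two procedures in each of two sets.

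The procedures are not interchangeable. The t test on change addresses the stated hypothesis directly. A repeated-measures ANOVA over several visits addresses a group effect averaged over visits, or any departure from parallel profiles. The sets can also diverge, since PP drops women lost after week 8 even though the primary endpoint is at week 8.

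Two things are at stake. A disagreement among the four results could not be settled from the text. A favourable one could also be chosen afterwards, with a false-positive rate above 5%. Objectives makes efficacy on VAS the primary objective, and the Discussion expects the trial to be the basis for a full RCT, so an ambiguous or false signal would carry forward.

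**Working it through.** **1. The plan's own figure.** Sample size calculation gives a difference of 11.85, SD 15.255, 13% dropout and a two-sided hypothesis; the 5% level is in Efficacy assessment. Power is not stated, so 80% is assumed.

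n per arm = 2 × [(1.96 + 0.8416) × 15.255 / 11.85]² = 26.0, and 26.0 / 0.87 = 29.9, so 30.

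The planned 30 per arm is reproduced. (Rounding up at each step gives 27, then 32.) The sizing therefore fits one two-sided 5% test.

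**2. Bounds on the error rate.**

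- If all four results had to be significant, the rate could not exceed that of any one test, so at most 5%.
- If any one sufficed and the tests were independent: 1 − 0.95² = 9.75% for two tests and 1 − 0.95⁴ = 18.5% for four. The tests share data, so the actual four-test rate lies below 18.5%.

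**3. Simulation under no effect, any one result sufficing.** From the article: 30 per arm, 13% dropout, LOCF in ITT. Assumed: random dropout; PP as completers less a further 0% or 10%; exchangeable or AR(1) correlation of 0.3, 0.5 or 0.7; ANOVA on visits 2–4 or 2–5; t test taken as independent-groups. That makes 2 × 2 × 3 × 2 = 24 scenarios of 3,000 replicates each. The simulation standard error at 5% is √(0.05 × 0.95 / 3000) = 0.4 points.

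| Results that count | Rate across scenarios |
|---|---|
| t test, ITT only | 4.2–5.7% |
| t test, ITT or PP | 5.2–8.1% (21 of 24 above 6%) |
| t test or group-by-time, ITT only | 5.8–8.4% |
| Four tests, ANOVA on group-by-time (Greenhouse-Geisser) | 6.8–11.2% |
| Four tests, ANOVA on group main effect | 11.7–14.8% |
| Either ANOVA term, both sets | 13.1–18.5% |

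The group-by-time row splits into 6.8–10.3% for visits 2–4 and 9.4–11.2% for visits 2–5. Without the Greenhouse-Geisser correction it is 7.3–12.2%. Taking the between-group t test literally as paired, with arbitrary pairs, gave 10.7–10.8% for the group-by-time rule in the two scenarios run.

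**4. Where the excess comes from.** Take visits 2–5, exchangeable correlation 0.5 and no extra PP exclusions. The t test in ITT gives 4.8%, adding the t test in PP gives 6.3%, and adding the group-by-time ANOVA in both sets gives 9.5%. Reading the group main effect instead gives 12.9%. Under AR(1) correlation with the group-by-time term, the ANOVA's share falls to about half.

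**5. ANOVA restricted to visits 2 and 4.** Let c be a woman's change. Her deviations from her own mean are −c/2 and +c/2. With δ̂ the group difference in mean change and s² the pooled variance of c:

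F(group × time) = [n₁n₀/(n₁+n₀)] × (δ̂²/2) ÷ (s²/2) = [n₁n₀/(n₁+n₀)] × δ̂²/s² = t².

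This is the independent-groups t test exactly. The four results collapse to two, leaving only the ITT/PP duplication.

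**The case against.** The strongest case against has four parts.

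- **No success rule is written.** A reader might infer that whichever analysis reaches significance counts, and that the trial's real false-positive rate is therefore 10 to 12%. The document supports neither. It states no any-one rule, and a rule requiring agreement would keep the rate at or below 5%. The 10 to 12% band lies inside the plausible range but is too narrow, because it fixes inputs that the article leaves open. This objection stands, so the size can only be conditional.
- **The problem is not fully separate from the ANOVA specification.** A reader might infer that it would persist unchanged once the t test is made independent and the ANOVA given the right contrast. It would not: on visits 2 and 4 the two procedures coincide. Only the missing ITT/PP ranking would remain, worth about 6 to 8%. This stands too.
- **Running both ITT and PP is ordinary practice**, and ranking them may be left to a fuller document. True, and the use of both sets is not criticised here. But the article goes beyond silence: it assigns two different procedures to one hypothesis at one level.
- **This is a pilot with a feasibility aim.** That limits the weight. It does not remove the point, because the article also makes efficacy the primary objective and states a formal hypothesis.

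**Conclusion.** The structural point holds. One primary hypothesis has two between-group procedures in two unranked sets, all at P < 0.05, so the text neither secures its 5% level nor settles a disagreement.

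The size is conditional. If any one significant result were called a positive primary finding, the rate would be roughly 7 to 15%, and up to about 18% if either ANOVA term were accepted. This rests on assumed correlations, random dropout, assumed PP losses, and the ANOVA term and visits that the article does not give. The switch to nonparametric tests for non-normal data was not simulated.

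Most of the excess generally comes from the ANOVA's open visits and term rather than from using both sets. The point should be corrected, but it does not undermine the design.

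**What to change.** State in Efficacy assessment that the primary conclusion rests on one analysis: the two-sided 5% independent-groups comparison of VAS change from visit 2 to visit 4 in the ITT set. Replace the word paired for this between-group test. Label the PP analysis and the all-visit repeated-measures ANOVA as supportive, reported with estimates and 95% confidence intervals, and unable to establish efficacy if the primary test is not significant.

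This takes one or two sentences before database lock, with no extra data or participants. One named test in one set returns the rate to 5% (simulated 4.2–5.7%), and 30 per arm stands. The small cost is that a significant PP or ANOVA result alone can no longer be called a positive primary result.

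### LOCF, the stated ITT method for missing data, can bias the week 8 VAS difference in either direction and treats imputed values as observed

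*Protocol article*

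**What the plan says.** Under Statistical analysis, Efficacy assessment, the protocol article fixes the method: "Missing data will be adjusted using the last-observation-carried-forward (LOCF) imputation method on ITT analysis". It names no other missing-data method. The ITT set is everyone randomised: "The ITT method will include all randomly assigned subjects, regardless of any protocol violations or study dropouts". A per-protocol analysis is also planned, but on a different set: "The PP method will include only the subjects who have completed the 12-week study period without any major protocol violations", with compliance of at least 70%.

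The section headed Primary outcome measure defines the endpoint: "The change in the VAS score between visit 2 (baseline) and visit 4 (after treatment) will be used as the primary outcome measure". On timing, "The VAS score will be measured at every visit". By Table 4, that gives one value between baseline (visit 2, day 0) and the endpoint (visit 4, day 56), namely visit 3 at day 28.

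Table 3 lists eight grounds for withdrawal. They include compliance below 70%, a serious adverse event, and "Those who need standard treatment due to deterioration of symptoms of CHHF". The text above that table adds: "The subjects who are withdrawn after randomization will be followed up for outcomes". The article does not say how those later outcomes enter the week 8 analysis.

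**The concern.** LOCF assumes that a woman's VAS stays where it was last seen. With one intermediate visit, the assumption is crude: a woman lost before visit 3 is given zero change, and a woman lost after it is held at week 4 whatever happened next. Several withdrawal grounds are linked to outcome or tolerability. A woman who leaves because her symptoms worsened may be scored at a value taken before she worsened.

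The size and sign of the error depend on how many women each arm loses, when and why they leave, and how VAS moves over time in both arms. LOCF is therefore not reliably conservative. The filled-in values are then analysed as if they had been measured. The per-protocol analysis is no check, because it leaves out the women whose values LOCF would fill.

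The result also has a further use. Under Sample size calculation, the trial is meant to supply the power calculation for a later large trial, so a distorted effect would carry over into that design.

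**Working it through.** **Inputs from the article (Sample size calculation).** Difference 11.85 on a 0–100 mm scale ("the expected average VAS score difference in the SDT group is 11.85", read here as the between-arm difference), SD 15.255, dropout 13%, 30 women per arm. The test is two-sided at 0.05. Power is not stated; 80% is assumed.

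**The plan's own figure.** n = 2 × (1.96 + 0.842)² × (15.255 / 11.85)² = 26.02 per arm. Then 26 / (1 − 0.13) = 29.9, so 30 per arm. The stated size is reproduced, which supports the reading of 11.85. (Rounding 26.02 up to 27 would give 32.)

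**LOCF mean in one arm.** Let m be the mean change at week 8, d the proportion with no visit 4 value and s the share of those lost after visit 3. Assume that half the change is reached by visit 3 (linear), that women who leave are average for their arm, and that nothing is recovered after withdrawal. Then

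LOCF mean = m × [(1 − d) + d × s × 0.5].

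**Equal dropout of 13%, true difference 11.85 mm.**
- Half lost before visit 3 (s = 0.5): 11.85 × (0.87 + 0.0325) = 10.7 mm.
- All lost before visit 3 (s = 0): 11.85 × 0.87 = 10.3 mm.
- At a fixed SD, planning the next trial on these would raise its sample size by (11.85/10.7)² − 1 = 23% or (11.85/10.3)² − 1 = 32%.

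**No true effect, unequal dropout.** These figures are assumptions not in the article: 15 mm improvement in both arms; dropout 20% on SDT and 6% on placebo (average 13%).
- s = 0.5: SDT 15 × 0.85 = 12.75; placebo 15 × 0.955 = 14.33; false difference 1.6 mm against SDT.
- s = 0: 12.0 against 14.1; false difference 2.1 mm against SDT.
- With SE = 15.255 × √(2/26) = 4.23 mm, this is 0.4 to 0.5 of a standard error. Swapping the dropout rates swaps the sign.

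**Outcome-dependent dropout.** The formula treats dropout as unrelated to outcome, so it was supplemented by simulation (30 per arm, 4,000–5,000 runs per scenario). Assumptions not in the article: placebo improvement of 10 or 0 mm; half the change reached at week 4; correlation of changes 0.6; half of dropouts with a week 4 value; dropout at random or driven by a poor week 4 or week 8 score; rates 13%/13%, 20%/6% and 6%/20%, plus 26%/0% under no effect.
- True effect 11.85: LOCF gave 9.2 to 12.1 mm. Where power was tallied it was 0.71 to 0.81, against about 0.84 with complete data.
- No effect, equal dropout: no bias; type I error 0.048.
- No effect, unequal dropout: from 1.8 mm in favour of SDT to 1.3 mm against it. The highest type I error was 0.071 (26% v 0%, at random).
- Half of the withdrawn women recovered by follow-up (13%/13%, driven by week 8): LOCF gave 11.2 mm, against 10.7 mm with none recovered.
- A likelihood estimate assuming missing at random gave about 11.9 mm with 13% lost per arm at random or on week 4 scores. With dropout driven by week 8 itself and unequal by arm, it gave 9.9 or 13.8 mm. LOCF gave 11.1 and 10.2 mm in those two scenarios.

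**Precision.** Counting all 30 per arm as observed gives a nominal SE of 15.255 × √(2/30) = 3.94, 7% below the 4.23 for 26 observed. Simulated LOCF standard errors nonetheless tracked the LOCF estimate's own sampling SD (for example 3.97 v 3.98).

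**The case against.** A reader might infer that the week 8 effect is certain to be biased and its standard error understated. The article does not support that. Dropout by arm is unknown, the bias can take either sign, and it vanishes with no effect and equal dropout. The standard error is modestly smaller than 26 observed women per arm would support, but it is not clearly miscalibrated for the LOCF estimate. What remains is that imputed values are treated as observed.

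A reader might also take the planned follow-up of withdrawn women as part of the cause. It works the other way: LOCF applies to missing data, a collected outcome is not missing, and nothing says that LOCF overwrites it. That stands, and it makes the figures that treat all 13% as lost an upper illustration. What is open is whether and how those outcomes are used.

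The 15 mm improvement and the 20% v 6% split are illustrative, and even then the false difference is at most half a standard error in a 60-woman pilot. Sensitivity analyses may stand in a separate analysis plan. The article nonetheless states LOCF as the ITT method, so this is a stated choice and not an omission.

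Finally, a missing-at-random model is no full cure. In the two simulated scenarios where it went wrong, LOCF lay nearer the truth, through offsetting errors that cannot be relied on. This objection stands, and the fix must answer it.

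**Conclusion.** The point holds in this form: the stated ITT method can misstate the week 8 difference in either direction, because only one post-baseline visit precedes the endpoint and withdrawal is partly linked to outcome. At the planned 13% dropout in both arms, the planned difference shrinks by about 1.2 to 1.5 mm (11.85 to 10.7 or 10.3), given a linear effect, average dropouts and no recovered values. Where the arms lose different proportions, a spurious difference of about 1.6 to 2.1 mm is possible under the assumed figures. The problem is smaller the more post-withdrawal VAS values are collected and used. The effect on precision is modest and is not the main reason for a change.

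**What to change.** 1. State that VAS values collected after withdrawal enter the ITT analysis as observed. Note that the estimate then includes the effect of any other treatment received after withdrawal.
2. For values that are truly missing, make the main analysis a likelihood-based mixed model (visits 3 and 4, treatment-by-visit interaction, baseline VAS, hospital) or multiple imputation.
3. Add a sensitivity analysis for dropout that depends on the unseen outcome, for example imputation with a delta adjustment varied separately by arm.
4. Keep LOCF at most as a further sensitivity analysis.

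The cost is a change of analysis wording and slightly more programming. The named software, SPSS 23, fits mixed models. No extra visits or measurements are needed. Recruitment was still open when the article appeared, and analysis follows database lock, so the change can be fixed before the data are analysed.
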